### Ethics, data privacy and participant safety

2.8

The ReMindCare app project has received full approval from the Research Ethics Committee of the faculty of Medicine at the University of Valencia and from the Research Ethics Committee of the Sanitary Research Institute (INCLIVA) of the Clinical Hospital of Valencia, Spain.

To protect the data sent by patients, communications to the platform are encrypted with a transport layer security certificate from the Generalitat Valenciana and are sent through the HTTPS (Hypertext Transfer Protocol Secure) protocol. This process ensures that all transmitted data are completely private and without a chance of being manipulated. Moreover, the hospital infrastructure is protected through a reverse proxy, which enhances security by establishing a single access point to it and hiding all inner infrastructures. Moreover, the integration of the app into the hospital systems is subjected to the LOPD‐GDD (Organic Law 3/2018: protection of personal data and digital rights guarantee, December 5th), the Spanish organic law adaptation of the GDPR (General Data Protection Regulation).

## RESULTS

3

The ReMindCare app was systematically introduced into clinical practice in October 2018, and 57 patients have been enrolled in the study since then. Updates of the app and improvements in its functioning will be conducted as requested by feedback obtained from patients and clinicians and in accordance with Android and iOS developments.

## DISCUSSION

4

ReMindCare is an e‐health intervention aimed at improving the quality of the current programme for early treatment of patients with psychosis. Although there are an increasing amount of apps being studied for early course psychosis (Camacho, Levin, & Torous, 2019), to our knowledge, this is the first pragmatic and prospective integration of an app into real world clinical care. The study is thus designed to generate data beyond just how the app may improve care but also how it can be implemented into clinical care, leading to the ability to augment quality existing health services (Bonet et al., 2017).

### Anticipated results

4.1

On the basis of previous studies (Bonet et al., 2017; Firth et al., 2016; Gitlow et al., 2017) that confirmed the interest of patients with psychosis in e‐health interventions and based on the high interest in owning an e‐health app that we found in our survey study (Bonet et al., 2018), we expect an acceptable retention rate (beyond 70%).

Moreover, based on previous studies (Ben‐Zeev et al., 2014; Ben‐Zeev, Kaiser, & Krzos, 2014; Brenner & Ben‐Zeev, 2014; Kimhy, Vakhrusheva, Liu, & Wang, 2014; Macias et al., 2015) that found rates of response to the communications of e‐health apps to be higher than 70%, we also expect moderate compliance with the app's communications (beyond 70%).

Furthermore, as previous studies have stated that electronic assessments are valid and reliable measures (Brenner & Ben‐Zeev, 2014; Kimhy et al., 2014; Palmier‐Claus et al., 2013; Spaniel et al., 2008), and based on preliminary perceptions obtained from the first 7 months of the current intervention, we expect that the use of the ReMindCare app would produce the following differences in the treatment of psychotic disorders:
*Improved quality of treatment delivery for clinicians*: Graphics of daily and weekly questionnaires allow clinicians to rapidly assess the status of the patient and to specifically orient their interactions with the patient to problematic areas. An improvement in the quality of evaluation is also expected. Perceptions of the clinicians regarding these issues will be qualitatively assessed in focus groups.
*Improved insight about the illness and mental health status for patients*: Sharing with patients their responses to the app is expected to increase accuracy of information and to decrease bias in this process. Moreover, it is expected that, by discussing their app responses with the patients, insight about their illness and their health status will increase. These perceptions will be mainly assessed by the “satisfaction questionnaire” (SQ), and they will also be assessed qualitatively in focus groups. Moreover, changes in insight between baseline and 1 year of intervention will be assessed by using the BCIS (Beck et al., 2004).
*Improved quality of communication between patient and clinician*: It is expected that patients will feel more understood as a result of improvements in evaluation and quality of their interactions with the clinician, which could lead to an enhancement of the overall quality of communication and alliance between patient and clinician. Again, this will be assessed by the SQ and the focus groups.
*Improved adherence to treatment for patients*: As a result of improvements in insight about the illness and improvements in alliance with clinicians, an enhancement of adherence to treatment is also anticipated. Significant differences are expected in the SMAQ (Hogan et al., 1983) scores of patients between baseline and 1 year of intervention. Moreover, the number of relapses, treatment dropouts and rates of compliance and adherence to ReMindCare tests will also be analysed in this regard. It is expected that the more patients use ReMindCare (high rates of engagement and compliance), the fewer treatment dropouts and relapses there will be.
*Improved early relapse detection and hospital admission reduction*: Again, higher rates of engagement with ReMindCare are expected to produce lower hospital admissions, early detection of relapses and fewer visits to urgent care units. Moreover, rates of relapses, changes in medication and visits to urgent care units will be compared among patients who used the “urgent consultation” function and those who do not. We expect that using this function will improve the quality of early detection.
*Improved quality of communication between health care providers and improved quality of treatment decisions*: Due to general access of health care professionals to ReMindCare reports on the EMR, we expect improved communication between health professionals and, because of this, improved quality of treatment. Perceptions of clinicians on this issue will be qualitatively assessed in focus groups.

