## INTRODUCTION

1

Early intervention programs for first‐episode psychosis are effective evidence‐based interventions that foster recovery, prevent disability and reduce costs associated with illness in both the short and long term (Arango et al., 2017). However, like all clinical programs, they face implementation challenges. Specific challenges identified by the RAISE study in the United States include workforce development, community activation, fidelity and measurement of outcomes and patient involvement (Dixon, 2017). In Spain, which has a non‐contributory health system financed through taxation and supported by public funding, universal health coverage and free health care services result in a lack of professionals, tools and financial support to properly deliver these interventions (Arango et al., 2017). Thus, interventions that reduce the number of consultations and hospital admissions, enhance interview efficiency, increase the early detection of illness and enhance treatment efficacy are highly encouraged (Arango et al., 2018; MSCBS, 2019). Research on smartphone ownership among youth receiving early intervention services suggests that, like the rest of the population, they increasingly own these devices; a 2015 study suggested 81% ownership (Lal et al., 2015), and more recent research studies suggested 85% (Aref‐Adib et al., 2016) to 86% (Bonet et al., 2018) ownership. Furthermore, many studies have found high percentages of interest (70%‐80%) in e‐health interventions among these patients (Bonet et al., 2017; Firth et al., 2016; Gitlow et al., 2017), with no differences related to demographic or clinical characteristics (Berry, Lobban, Emsley, & Bucci, 2016; Bonet et al., 2018).

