### Study objectives

2.1

The main objective of this study is to address whether the introduction of the ReMindCare App into daily clinical practice improves the quality of treatment for patients in a first episode of psychosis programme (FEPP).

Specifically, the aims of the study are (1) to assess the effectiveness of the ReMindCare app, in terms of improvement of adherence to anti‐psychotic medication, early detection of relapses and improvement of communication with clinicians, vs treatment as usual in patients with a psychotic disorder; (2) to analyse the use of the ReMindCare app by the patients in terms of rates of adherence, compliance, alerts generated and the total time using the app; and (3) to assess the satisfaction of patients with using the app and the perceived usability of the ReMindCare app.

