#### Eligibility criteria

2.4.2

To be considered for this study, patients must be accepted into the FEPP at the Clinical Hospital of Valencia. Criteria for inclusion in the FEPP are:Diagnosis of psychotic disorder following DSM‐5 (APA, 2013) criteria, interview conducted by a licensed clinician.Less than 5 years of illness duration.Residence associated with the hospital area of correspondence (Area 5 of Valencia).Age between 17 and 65 years oldOwnership of a smartphone with an internet connection that allows the proper installation and functioning of the app.

Exclusion criteria include the following:Inability to use and master a mobile device and the Internet.Refusal to sign an informed consent form.Spanish/English language fluency limiting ability to partake in clinical conversations or to understand the app questionnaires.

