Baseline surveys, including clinical and sociodemographic information and clinical standardized questionnaires, were administered before the enrolment of the patient in the study. As shown in Table 1, data regarding the main outcomes, such as adherence to medication, number of relapses, number of visits to the hospital urgent care units and number of hospital admissions, will be collected and analysed at the end of the first, second and fifth years of the intervention. Moreover, information generated for patients through the use of the app will also be analysed at the same timepoints. Finally, to analyse the feedback of patients regarding the use of the app, we plan to conduct focus groups at the end of the first year of the intervention, and we have also designed a “satisfaction questionnaire” (SQ) that patients will complete at the end of the first year of the intervention or before discontinuing the use of the app (if discontinuation occurs before the first year of app usage). This SQ was made for the purpose of this research study and is based on previous satisfaction and usability questionnaires, such as the user version of the Mobile Application Rating Scale (uMARS) (Stoyanov, Hides, Kavanagh, & Wilson, 2016), the System Usability Scale (SUS) (Brooke, 1996), EnLight: a tool for mobile and web‐based eHealth interventions (Baumel, Faber, Mathur, Kane, & Muench, 2017) and the App Quality Evaluation (AQEL) (DiFilippo, Huang, & Chapman‐Novakofski, 2017). This questionnaire is displayed in Appendix B.

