### Planned data analysis

2.7

Descriptive analyses of sociodemographic and clinical variables will be conducted. A multivariate data analysis will be carried out to explore relationships between sociodemographic and clinical variables and adherence to treatment and ReMindCare measures. An ANOVA model of repeated measures will be used for the main research outcomes. All analyses will be conducted with an alpha set at *P* < 0.05.

These preliminary quantitative data analyses and the preliminary results regarding patient compliance, retention rate and perceived satisfaction with the use of the ReMindCare app are expected by the end of the first year of using the app (March 2020). At that time, qualitative analyses of data are also planned.

Subsequent analysis of the data will be conducted at the end of the second and fifth years of use of the app.

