However, some limitations must be taken into consideration. First, because of the characteristics of this real‐world intervention, our study is not randomized or controlled. However, we plan to compare the main outcomes of the use of the app between users and age‐matched controls, although the groups may differ in some characteristics. Another limitation is that ReMindCare has only been designed for Android systems, although an iOS version of the app is being designed.

To our knowledge, this is one of the earliest e‐health interventions for patients with psychosis implemented as a standard care tool integrated into clinical practice in the public hospital workflow. Real‐time health information is being collected and used to work together with patients to improve the quality of real‐world health care delivery.

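### The one SMAQ contrast spelled out for adherence is an uncontrolled within-user change over year 1, which cannot answer the treatment-as-usual aim; the announced control comparison should carry that conclusion

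*Protocol article*

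**What the plan says.** All references are to the protocol article.

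- **Aim.** Section 2.1 sets the effectiveness aim, with adherence to antipsychotic medication as its first component, "vs treatment as usual in patients with a psychotic disorder".
- **Outcome.** Section 2.6 refers to "data regarding the main outcomes, such as adherence to medication, number of relapses", so adherence is a main outcome. Table 1 measures it with the SMAQ at baseline, year 1, year 2 and year 5.
- **Expected evidence.** Section 4.1 opens its list with "we expect that the use of the ReMindCare app would produce the following differences in the treatment of psychotic disorders". Under adherence it anticipates significant differences in the SMAQ "scores of patients between baseline and 1 year of intervention". No comparator is mentioned there.
- **Model.** Section 2.7 states: "An ANOVA model of repeated measures will be used for the main research outcomes". No group factor is named, and Table 1 shows a schedule for the ReMindCare intervention only.
- **Population.** Section 2.4.1 makes every eligible FEPP outpatient a potential user. Section 2.4.2 requires "Less than 5 years of illness duration". The Introduction says: "Early intervention programs for first‐episode psychosis are effective evidence‐based interventions that foster recovery".
- **Controls.** Section 4.2 concedes that the study is neither randomised nor controlled, then adds: "we plan to compare the main outcomes of the use of the app between users and age‐matched controls". It accepts that the groups may differ.

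**The concern.** The stated aim is a between-treatment question, but the only SMAQ contrast written out is a before-after change in people who all use the app. Those people are also all receiving the FEPP. For someone enrolled near programme entry, the first year of app use is also the first year of programme treatment. For someone enrolled with nearly 5 years of illness, it is a late and possibly stable, or declining, phase. Table 1 has one SMAQ before the app starts, so a patient's earlier trajectory cannot be seen and regression to the mean cannot be separated out.

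What is at stake is the reading of the year-1 result. A significant time effect could appear with an app that does nothing, and a real benefit could be hidden if adherence tends to fall over the interval. Neither result would answer the question posed against treatment as usual.

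**Working it through.** **1. Setting the sections side by side.** Write the users' mean SMAQ change from baseline to year 1 as

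change in users = app effect + drift in users,

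where drift collects programme effect, illness course and regression to the mean. The contrast in section 4.1 estimates the whole sum. Aim 1 needs the app effect alone. With controls,

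change in users − change in controls = app effect + (drift in users − drift in controls).

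The bracket vanishes only if the two groups drift alike. Age matching does not secure this where drift depends on illness duration and time in the programme.

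**2. No figure to reproduce.** The article gives no sample size target, no SMAQ effect or SD, and no usual-care SMAQ trend. Everything below is illustration under assumptions.

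**3. Inputs.**
- n = 57: enrolled so far (section 3), a running count and not a target.
- n = 40: 57 × 0.70 = 39.9, from the expected retention above 70% (section 4.1).
- Alpha 0.05 (section 2.7), taken as two-sided.
- App effect: zero.
- Assumed: SMAQ read as adherent or not, with about 35% of patients changing category.

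**4. Before-after test, binary reading.** McNemar statistic (b − c)²/(b + c) > 3.841, without continuity correction, where b patients improve and c worsen. The probability of rejection was obtained by exact enumeration of the multinomial.

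| Improve / worsen | Net drift (points) | Significant, n = 57 | Significant, n = 40 |
|---|---|---|---|
| 0.175 / 0.175 | 0 | 5% | 5% |
| 0.22 / 0.12 | +10 | 26% | 18% |
| 0.25 / 0.10 | +15 | 50% | 35% |
| 0.28 / 0.08 | +20 | 75% | 57% |

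Reversing the drift to −10 points (0.12 / 0.22) gives a significant improvement in about 0.1% of studies at either n. A downward drift does not produce false benefit; it works against detecting a real one.

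**5. Before-after test, continuous reading.** The article speaks of scores and plans an ANOVA, so the check was repeated with a paired t-test. The noncentrality is g√n, where g is the assumed drift in SDs of the change score.

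| g | n = 57 | n = 40 |
|---|---|---|
| 0 | 5% | 5% |
| 0.1 | 11.5% | 9.5% |
| 0.2 | 31.7% | 23.5% |
| 0.3 | 60.5% | 45.7% |

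**6. User-versus-control difference in change.** Two-sample t-test with equal groups (assumed). The noncentrality is r√(n/2), where r is the difference in drift between the groups, in SDs of change.

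| r | 57 per group | 40 per group |
|---|---|---|
| 0 | 5% | 5% |
| 0.2 | 18.5% | 14.3% |
| 0.3 | 35.5% | 26.3% |

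Shared drift cancels whatever its size. Drift that differs between the groups does not, hence the need to align and adjust for more than age.

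**The case against.** The strongest reply is that the control comparison is already planned. Aim 1 names treatment as usual, section 2.6 makes adherence a main outcome, and section 4.2 plans to compare the main outcomes with age-matched controls while admitting the lack of randomisation. This stands. A reader might infer that the adherence claim rests wholly on the before-after change, and the article does not support that reading. Section 4.1 also plans to relate extent of app use to dropouts and relapses, so the SMAQ change is not the only evidence listed under adherence.

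Second, the SMAQ sentence states an expectation in the Discussion, not a decision rule, and a one-line ANOVA description does not exclude a group factor. A condensed article may leave model terms to a fuller document, so the missing group term is not counted as an error here. What remains is that the article does write out a specific contrast, attributes it to the app, and that contrast does not estimate the aim.

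Third, nothing in the article shows that adherence rises under the programme. The Introduction calls such programmes effective, which is not a statement about SMAQ trends. This also stands: the direction of drift is unknown, and late entrants may be stable or losing adherence.

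Fourth, the illustration depends on assumed drift, a binary reading and a running count. That is true; it shows sensitivity and does not predict a result.

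**Conclusion.** The point holds in a limited form. The SMAQ contrast given in section 4.1 is uncontrolled, is presented as something the app would produce, and cannot answer the treatment-as-usual aim in section 2.1. The comparison that could answer it appears only under limitations in section 4.2, is not carried into sections 2.7 or 4.1, and matches on age alone.

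A reader might go further and infer that ordinary improvement under the programme will be credited to the app. The documents do not support that certainty: they give no usual-care trend, and the bias could run either way. The 26% to 75% range at n = 57 (18% to 57% at n = 40) applies only with no app effect, a background gain of 10 to 20 points, and about 35% of patients changing category. With no drift the test keeps its nominal 5%.

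This should be corrected before a year-1 SMAQ change is reported as evidence of effectiveness.

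**What to change.** In sections 2.7 and 4.1, state that the adherence conclusion rests on the difference in SMAQ change between users and the controls announced in section 4.2. Measure it over the same interval since FEPP entry and adjust for baseline SMAQ and years of illness, both of which are in Table 1 for users. Label the within-user change from baseline to year 1 as descriptive.

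**Cost.** The change is mainly one of wording. Controls need the SMAQ and years of illness at matching times, and time since FEPP entry must be known for both groups. The estimate is less precise: with equal groups and equal SDs of change, the variance of the difference is 2σ²/n against σ²/n for the within-user mean, so the standard error is √2 ≈ 1.41 times as large. Adjustment reduces, but cannot exclude, residual differences between non-randomised groups, so the caveat in section 4.2 should stay.

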**FIGURE 1 eip12960-fig-0001:**
[figure not shown]
Screen shot of the ReMindCare dashboard (App for patients). Example of daily evaluation questions

To use this clinical tool, clinicians enrol their patients via a private portal. Once the patients are registered into the portal, they can download the app, which is available on “Google Play,” log into the app and begin to use it. Patients are instructed on how to download and log into the app, and they are informed regarding how their app data are used.

The information gathered by the app is accessible to clinicians on the portal, and it is exclusively used to orient clinicians for upcoming visits with patients, to help both patients and clinicians have a shared vision of the status of the patient and to discuss and establish together the therapeutic approaches. In addition, as displayed in Figures 2 and 3, on this portal, clinicians can not only visualize the information but also generate a PDF report that summarizes this information. These reports can be uploaded to the electronic medical record (EMR) of the patient because we enabled a function in the electronic hospital system that allows the inclusion of the ReMindCare app reports as another type of clinical report (eg, similar to results from a blood pressure test or glucose test). Moreover, if patients do not respond to notifications or abrupt variation in their answers occurs, the system automatically generates “alarms or warnings.” These alarms notify the clinician by e‐mail and are also displayed in the profile of the patient on the website. Moreover, patients are able to contact their clinician using an “Urgent Consultation” tab displayed on the app if they detect a significant worsening in their health status. By clicking this button, clinicians receive a notification e‐mail and have to contact the patient within a maximum period of 48 hours. Further information about the use of the app and the webpage is available in the user manual included in Appendix A.

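### Comparing outcomes between users and non-users of the urgent-consultation button is confounded by indication: it can make a helpful or neutral function look harmful and cannot support the early-detection claim

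*Protocol article*

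**What the plan says.** - **The comparison.** Section 4.1 (Anticipated results), in the item on early relapse detection and hospital admissions, states that "rates of relapses, changes in medication and visits to urgent care units will be compared among patients who used the" urgent-consultation function and those who do not use it.
- **The reading placed on it.** The next sentence is "We expect that using this function will improve the quality of early detection".
- **What leads to a press.** Section 2.5.2, in the text after Figure 1, describes a "tab displayed on the app if they detect a significant worsening in their health status".
- **What follows a press.** The same paragraph says that clinicians receive an e-mail and "have to contact the patient within a maximum period of 48 hours".
- **Adjustment.** Section 2.7 offers this: "A multivariate data analysis will be carried out to explore relationships between sociodemographic and clinical variables" on one side and treatment adherence and app measures on the other. It also names a repeated-measures ANOVA for the main outcomes. Neither is tied to the button comparison.
- **Acknowledged limits.** Section 4.2 concedes that "our study is not randomized or controlled". It adds "although the groups may differ in some characteristics", but this concerns app users against age-matched controls, not patients who pressed the button against those who did not.

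**The concern.** The exposure is defined by a precursor of the outcome. A patient joins the user group by noticing a deterioration, and deterioration is also what leads to relapse, a change of medication or an urgent visit. Splitting patients by button use therefore largely splits them by whether they got worse.

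There is a second difficulty with two of the three outcomes. The clinician must respond to each press, so a medication change or an urgent visit may be a direct result of that contact. More of these events among users could mean that the function worked, or that it did not. The article does not say which direction would count in its favour.

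At stake is how a patient-initiated safety function is reported. A raised crude ratio could be taken as evidence against a function that helps. A ratio near 1 could hide a substantial benefit.

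**Working it through.** The article states no event rate, effect size or power for this contrast, so there is no figure to reproduce. The direction and possible size of the bias can be examined with a two-stratum model. Every rate below is an assumption; none comes from the article.

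**Inputs**
- w = proportion of patients who worsen: 0.25
- a = probability that a worsening patient presses: 0.60
- b = probability that a stable patient presses: 0.10
- r1, r0 = relapse risk without a press in worsening and stable patients: 0.50 and 0.10, then 0.30 and 0.10
- θ = true risk ratio of the function, the same in both strata: 1 (no effect) or 0.5 (halves relapse)

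**Formulas**
- Risk in users: Ru = θ[w·a·r1 + (1−w)·b·r0] / [w·a + (1−w)·b]
- Risk in non-users: Rn = [w(1−a)r1 + (1−w)(1−b)r0] / [w(1−a) + (1−w)(1−b)]
- Crude ratio = Ru/Rn

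**Group composition**
- Users: 0.25×0.60 = 0.150 worsening and 0.75×0.10 = 0.075 stable, total 0.225. Two thirds of users are worsening patients.
- Non-users: 0.25×0.40 = 0.100 worsening and 0.75×0.90 = 0.675 stable, total 0.775. About 13% are worsening patients.

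**Relapse risks 50% and 10%**
- Users, θ = 1: (0.150×0.50 + 0.075×0.10)/0.225 = 0.0825/0.225 = 0.367
- Non-users: (0.100×0.50 + 0.675×0.10)/0.775 = 0.1175/0.775 = 0.152
- Crude ratio: 2.42 with no effect; 0.5×2.42 = 1.21 when relapse is halved

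**Relapse risks 30% and 10%**
- Users, θ = 1: (0.150×0.30 + 0.075×0.10)/0.225 = 0.0525/0.225 = 0.233
- Non-users: (0.100×0.30 + 0.675×0.10)/0.775 = 0.0975/0.775 = 0.126
- Crude ratio: 1.85 with no effect; 0.93 when relapse is halved

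In this model the crude ratio is θ times the no-effect ratio. To look merely neutral, the function would have to cut relapse by 1 − 1/2.42 = 59% in the first case and by 1 − 1/1.85 = 46% in the second.

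**Other assumptions**
- With w = 0.30, a = 0.60, b = 0.05, risks of 50% and 10%, and θ = 0.70, the crude risks are 30.4% and 16.1%, a ratio of 1.89. Comparing within the worsening and stable strata returns 0.70.
- Keep θ = 0.70 and vary w over 20–40%, a over 40–80%, b over 2–10%, and the risks over 30%/10%, 50%/10% and 60%/5%. The crude ratio is above 1 in all 81 combinations, from 1.06 to 5.02, with a median of 1.75.
- If worsening patients pressed less often than others (10% against 30%, with w = 0.30 and risks of 50% and 10%), a function with no effect would give 0.62. That pattern runs against the use described in section 2.5.2.

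**The case against.** **It is a minor comparison.** It is one sentence in the discussion. It does not appear in section 2.7, and request counts are not among the main outcomes in section 2.6. The repeated-measures analysis and the age-matched comparison do not depend on it. This stands and limits the consequence. However, the article itself fixes the groups, the outcomes and the interpretation, so the flaw is not a detail left to an analysis plan.

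**No direction is stated.** The article expects better early detection and does not say that users will have fewer events in this contrast. More medication changes could be read as success. This also stands, but an outcome that can be read either way does not support the claim any better.

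**The size is unknown.** A reader might infer that users will almost surely show more relapses whatever the button does. The documents do not support that. With the same 25%/60%/10% inputs, the ratios reach 5.2 (no effect) and 2.6 (relapse halved) only if every worsening patient relapses and no stable patient does. Under milder risks a halving function falls to 0.93. Patients who worsen without noticing would also sit among the non-users.

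**Timing.** A reader might infer that relapses before the press will be counted against users. The article states no time window in either direction, and a fuller document may set one.

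**Conclusion.** The concern holds as a matter of design. By the article's own description, button use follows self-detected worsening, and no stated adjustment or caveat covers this contrast. It can make a helpful or neutral function look harmful, and it cannot support the early-detection claim.

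The size cannot be derived from the document. Under the stated assumptions, a function with no effect gives a crude ratio of about 1.85 to 2.4, and one that halves relapse gives about 0.93 to 1.2. In the more favourable case the function does not look harmful, but a true ratio of 0.5 is almost entirely hidden. The direction rests on patients using the button as section 2.5.2 describes. The magnitude rests on assumed rates of worsening, pressing and relapse.

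**What to change.** **Minimum change.** State that the ever-used versus never-used table is descriptive and that no inference about the function's effect will be drawn from it. This costs one sentence and needs no new data.

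**If an effect is to be explored:**
- Define worsening episodes independently of the outcome, from app alarms or the weekly prodromal and daily ratings. Do not define them by relapse: relapses that the function averted would drop out of the denominator.
- Compare later relapse or admission after episodes with and without a request.
- Count only events after the request, and set a corresponding start of follow-up for episodes without one.
- Adjust for the scores preceding the episode.
- Treat medication changes and urgent visits as ambiguous, because they may follow directly from the required contact.

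**Cost.** Table 1 lists numbers of requests, relapses, visits and admissions, not their dates. The sponsor must confirm that request and event dates can be retrieved from the app logs and the medical record. Precision will be poor. With the 57 patients enrolled so far and the assumptions above, about 57×0.25 = 14 patients would worsen, roughly 9 with a request (57×0.150) and 6 without (57×0.100). Adjustment may be barely feasible at that size. Residual confounding will remain, so the result should be labelled exploratory.
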